### Outcomes

2.6

The primary system-level outcome is the incremental cost per quality-adjusted life-year (QALY), estimated using the EQ-5D-5L, incorporating costs from both a healthcare payer and a societal perspective [43]. Direct medical costs over 12 months will be collected through a structured patient-reported healthcare utilization questionnaire administered at each follow-up time point, capturing GP consultations, physiotherapy, specialist visits, investigations (imaging, blood tests), medications, injections, surgery, and hospitalization, previously used in Switzerland [28]. Where available, self-reported data will be complemented and validated using health insurance reimbursement data provided by the main healthcare insurances in Switzerland, covering patients insured by this provider. Indirect costs related to absenteeism and presenteeism will be assessed using the Work Productivity and Activity Impairment Questionnaire (WPAI) [44,45].

The primary practitioner-level outcome is the proportion of patients receiving back-related imaging within 6 months of the initial consultation [29,35]. Secondary practitioner-level outcomes include opioid prescription, medication use, imaging rates and total number over 12 months, clinicians’ beliefs about LBP (measured with the 10-item Back Pain Attitudes Questionnaires, Back-PAQ), and confidence in managing LBP [[46], [47], [48], [49]].

The primary patient-level outcome is back-related disability measured by the 24-item Roland–Morris Disability Questionnaire (RMDQ) at 6 months [50]. Secondary patient-level outcome measures include pain intensity (Numerical Rating Scale, NRS), health-related quality of life (EQ-5D-5L), work participation (WPAI), Global Rating of Change (11-point scale, GRC), pain self-efficacy (Pain Self-Efficacy Questionnaire short form, PSEQ-2), a range of psychological factors, including Fear of movement, Catastrophizing, Anxiety, Depression (Brief screening questions from Kent et al., 2014, BSQ), expectations to return to work (one question from Orebro questionnaire), beliefs about LBP (10-item Back-PAQ) and reassurance (Reassurance Questionnaire) [43,46,[51], [52], [53], [54]]. Based on the advice of our patient partner, two questions were added about capacity to perform valued activities and confidence in their back. PSEQ-2, BSQ and Back-PAQ questionnaires will help investigate the mechanisms of action of the PRIME intervention.

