### Statistical methods

2.12

Cost-effectiveness will be evaluated as the incremental cost-effectiveness ratio (ICER), expressed as net cost in CHF per quality-adjusted life-year (QALY) gained. QALYs will be derived from the EQ-5D-5L assessed at baseline and at 3, 6, and 12 months, using the French EQ-5D-5L value set [66], as there is currently no value set for Switzerland. QALYs will be estimated using the area-under-the-curve method over the 12-month follow-up, meaning that QALYs are calculated by multiplying the patients’ health state utility scores with the time spent in that health state.

Costs from the healthcare payer perspective will be estimated from self-reported healthcare utilization and, where available, health insurance data, applying current Swiss tariffs (TARDOC). The societal perspective will additionally include productivity losses due to absenteeism and presenteeism, assessed using the WPAI. Costs and QALYs will not be discounted given the one-year time horizon. Uncertainty will be assessed using non-parametric bootstrapping to estimate 95% confidence intervals for the ICER, and probabilistic sensitivity analyses will be conducted [67,68]. Cost-effectiveness will be explored across a range of willingness-to-pay thresholds.

Practitioner and patient-level outcomes will be analyzed according to the intention-to-treat principle by a blinded statistician. Primary and secondary continuous outcomes will be analyzed using linear mixed-effects models with random intercepts for clusters to account for the hierarchical structure of the data (patients nested within quality circles). Adjusted models will also be performed based on baseline variables (e.g. age, gender, socio-economic health determinants, RMDQ). Categorical outcomes (e.g. imaging prescription) will be analyzed using generalized linear mixed models [69].

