For patient-level primary outcome, an exploratory non-inferiority analysis will be performed using a margin of −2.5 points on the RMDQ, reflecting the possibility that the intervention may be acceptable if non-inferior and cost-saving. Pre-planned mediation analyses will examine the role of psychological factors in patient outcomes [70]. Different secondary analyses will be conducted, including the number of participants in each group that reach 30%, 50% and 70% of improvement on the RMDQ, as well as the number of participants reaching the patient acceptable symptom state (≤4 on RMDQ) [71]. All analyses will be performed using SAS (version 9.4) and Stata or R. Deviations from the statistical analysis plan will be documented and reported.

Given the three primary outcomes operating at distinct and complementary levels (system, practitioner, patient), findings will be interpreted jointly but are considered complementary rather than causally dependent. Each outcome is analyzed and reported independently, without formal alpha correction across levels. Discordant findings across levels are anticipated and theoretically meaningful: the three outcomes cover different domains serving different decision-making purposes, consistent with the GRADE Evidence to Decision framework [72].

Participants who withdraw or fail to complete baseline questionnaires will be considered screening failures and excluded from the trial. To ensure sufficient power at the primary endpoint, recruitment will continue until at least 200 patients per group have completed the 6-month assessment; consequently, total recruitment may exceed 500 participants. GP dropouts during the study period will not result in patient exclusion. Patient outcomes will be analyzed according to the cluster allocation at enrolment *(intention-to-treat principle)*.

For cost-effectiveness analyses, missing cost data will not be imputed; instead, they will be complemented where available with health insurance records. In case of discordance between data sources, patient questionnaire data will be considered primary and insurance data will be used for validation and to complement missing values. For outcomes other than costs, multiple imputation assuming data Missing at Random will be performed using SAS PROC MI for variables with more than 10% missing data, incorporating covariates, intervention group, and cluster information.

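### Missing costs may not be imputed while EQ-5D-5L data probably will be, so the two halves of the primary cost-per-QALY outcome follow conflicting missing-data rules

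*Protocol article*

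**What the plan says.** Section 2.6 makes cost-effectiveness one of three primary outcomes: "The primary system-level outcome is the incremental cost per quality-adjusted life-year (QALY), estimated using the EQ-5D-5L", from a payer and a societal perspective. On the cost side, "Direct medical costs over 12 months will be collected through a structured patient-reported healthcare utilization questionnaire administered at each follow-up time point". The follow-ups are at 10 days, 6 weeks and 3, 6, 9 and 12 months. Self-report is supplemented, where possible, by "health insurance reimbursement data provided by the main healthcare insurances in Switzerland, covering patients insured by this provider". The share of patients this reaches is not given.

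Section 2.12 derives QALYs from the EQ-5D-5L at baseline, 3, 6 and 12 months. For the second perspective, "The societal perspective will additionally include productivity losses due to absenteeism and presenteeism, assessed using the WPAI".

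The closing paragraph of Section 2.12 sets two rules for missing data:

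- Costs: "missing cost data will not be imputed; instead, they will be complemented where available with health insurance records".
- Everything else: "For outcomes other than costs, multiple imputation assuming data Missing at Random will be performed using SAS PROC MI for variables with more than 10%" of values absent, with covariates, intervention group and cluster in the imputation.

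Section 2.8 allows for 20% dropout and states that no sample size was calculated for cost-effectiveness.

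**The concern.** A cost-effectiveness ratio needs a cost and an effect for each patient, and the bootstrap around it normally resamples the two together. Here the cost half is left as observed and the effect half is imputed when the 10% trigger is met. This is a stated rule, not a detail left open.

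The rule makes the cost comparison depend on who answered the questionnaires and who is insured with a participating insurer. Unless it is adjusted in some way the article does not describe, a comparison of available costs is unbiased only if being observed is unrelated to cost within each arm, or if the distortion cancels between arms. That asks more of the data than the MAR assumption accepted in the same paragraph.

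The cost result also carries weight beyond its own outcome. Section 2.12 contemplates that PRIME could be acceptable if it is non-inferior on disability and saves money, so a distorted cost difference could tip the adoption decision.

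**Working it through.** **1. The plan's own figure.** Two arms of 10 clusters with 20 analysed patients each give 400. Allowing for 20% dropout, 400 / (1 − 0.20) = 500, as stated in Section 2.8. There is no corresponding figure for cost-effectiveness.

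**2. Which rule applies to which half.** The EQ-5D-5L is an outcome other than costs. If missingness is near the 20% allowance, it exceeds the 10% trigger (20% > 10%) and the utilities are imputed. Cost data are barred from imputation whatever the amount missing. So QALYs could be available for up to 500 patients and costs for fewer.

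**3. How many patients have costs.** Let m be the share of patients with incomplete self-reported costs and f the share of those that insurer records can complete. Patients with payer costs = 500 × (1 − m + m·f). m = 0.20 borrows the sample-size allowance; m = 0.30 and all values of f are assumptions.

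| m | f = 0 | f = 0.20 | f = 0.50 |
|---|---|---|---|
| 0.20 | 400 | 420 | 450 |
| 0.30 | 350 | 380 | 425 |

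Example: 500 × (0.80 + 0.20 × 0.50) = 450. If productivity costs are treated as cost data and nothing fills them, societal costs stay at 500 × (1 − m), that is 400 or 350.

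**4. What the ICER can then be.** Two readings fit the text:

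- Restrict the ICER to patients with costs. Pairs are intact, but the set is selected by response and insurer, and the imputed QALYs of the others are thrown away.
- Use every available value. Mean QALYs rest on up to 500 patients and mean costs on a subset of them, and some patients have no cost-effect pair to resample.

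**5. Items that fall under both rules.** Work participation measured by the WPAI is a secondary patient-level outcome (Section 2.6) and also the source of productivity costs. Imaging is the practitioner-level primary outcome and also a cost component. The same missing answer could be imputed for one analysis and barred from imputation in the other.

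**6. Illustration of bias.** Set the true mean cost to 1 in both arms, so the true difference is 0. Let p be the share still without costs and r the ratio of non-completers' to completers' mean cost. From 1 = (1 − p)c + p·r·c, the completers' mean is c = 1 / (1 − p + p·r). All values of p and r below are assumptions.

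| Pattern | c, arm A | c, arm B | False difference |
|---|---|---|---|
| p = 0.20 in both, r = 1.5 in both | 1/1.10 = 0.909 | 0.909 | 0% |
| p = 0.15 vs 0.25, r = 1.5 in both | 1/1.075 = 0.930 | 1/1.125 = 0.889 | about 4% |
| p = 0.20 in both, r = 1.5 vs 1.0 | 0.909 | 1.000 | about 9% |

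The distortion appears only when missingness, or the relative cost of non-completers, differs between arms.

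**The case against.** The best defence is that reimbursement records are real data and often preferable to imputed values. The article refers to the main insurers in the plural, so coverage could be broad, and Section 2.6 plans reminders, telephone contact and compensation to limit loss. Nothing in the document shows differential loss, and an incremental cost is a contrast in which equal distortions cancel. The analysis plan may also name the ICER analysis set.

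Much of this stands, and it rules out several stronger readings that a reader might infer:

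- That costs and QALYs come from different patients. The sets are either identical (restricted) or overlapping, and the text does not say which.
- That every other outcome is imputed. Only variables with more than 10% missing are.
- That the payer analysis is a pure complete-case analysis. Insurer filling prevents that to an unknown degree.
- That the societal perspective has no remedy. No back-up source is stated, but the WPAI as a secondary outcome falls under the imputation rule; whether its cost version does is ambiguous.
- That only about 62% of patients would have complete costs (0.80 × 0.95^5 = 0.619). This assumes 5% independent loss on each of five forms and that one missed form voids the total. It also carries the dropout allowance of a calculation built on the two 6-month outcomes to 12 months, and ignores insurer filling.

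What does not fall is the rule itself. Insurer records are used only where they exist, and whatever they leave missing may not be imputed. An analysis plan that follows the article inherits that bar.

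**Conclusion.** The concern holds in this form: a primary outcome is built from two quantities under conflicting missing-data rules, and the stricter rule leaves costs on a set selected by response and insurer. That the QALYs will be imputed is probable, not certain, since it depends on EQ-5D-5L missingness exceeding 10%.

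The size cannot be derived from the document. Under the assumptions shown, payer costs would be available for 350 to 450 of 500 patients, and the false cost difference would run from 0% to about 9% of mean cost. These figures illustrate and do not predict: insurer coverage, the 12-month response pattern and arm-specific missingness are all unknown, and recruitment may exceed 500. The document gives no evidence that bias will occur. It does fix a method that offers no protection if it does.

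**What to change.** Replace the no-imputation rule in Section 2.12 and carry the change into the analysis plan:

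1. Fill missing payer costs from insurer records first, as already intended.
2. Multiply impute the remaining costs, including WPAI productivity costs, jointly with the EQ-5D-5L utilities, by arm and respecting clusters.
3. Analyse costs and QALYs on the same intention-to-treat patients, and bootstrap them as pairs.
4. Report the available-case or complete-case ICER as a sensitivity analysis.

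The details of the imputation model, such as predictive mean matching for skewed costs, can stay in the analysis plan. The change needs wording and modest extra programming, and no new data. Its price is reliance on MAR for costs, which the protocol already accepts for its other outcomes. It does not alter the sample size, since none was calculated for cost-effectiveness.

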### Sample size

2.8

The sample size was calculated based on the primary patient-level outcome (RMDQ) and the primary practitioner-level outcome (imaging prescription rate) [61]. Assuming 10 clusters per group with a mean of 20 patients per cluster, the study has 80.97% power to detect a between-group difference of 2.5 points on the RMDQ (SD = 6.0), using an intracluster correlation coefficient (ICC) of 0.05 and a two-sided significance level of 0.05 [62]. The ICC of 0.05 and the 20% allowance for loss to follow-up were informed by Darlow et al. (2019), who used the same assumptions in a comparable cluster-randomized primary care study evaluating the RMDQ. For back-related imaging, the same cluster structure provides 81.99% power to detect a 15% absolute reduction from a baseline imaging rate of 30%, assuming an ICC of 0.01 [35,63]. Allowing for a 20% dropout rate, a total of 500 patients will be recruited (25 patients per cluster).

Variation in cluster size was assessed using the coefficient of variation approach [64]. Given a minimum of 15 and a maximum of 35 patients per cluster (mean = 25), the coefficient was < 0.23 and considered negligible. Therefore, no adjustment was applied, and recruitment will stop once a cluster reaches 35 patients. No formal sample-size calculation was performed for cost-effectiveness due to limited Swiss data. We aim to recruit at least 100 general practitioners (approximately five patients per GP) and a minimum of 30 physiotherapists.

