### Randomization

2.9

The 20 clusters will be randomly allocated to the intervention or control group (1:1). Allocation concealment is ensured by the use of a computer-generated random sequence held by a blinded statistician, with cluster allocation unknown to recruiters prior to randomization. Randomization will be stratified by cluster size (small vs large, defined by the median number of GPs per cluster) to ensure balance between study arms.

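### The planned SAS PROC MI imputation cannot carry the random quality-circle effect of the analysis model, so the standard error for the 6-month RMDQ will be moderately wrong, most likely too large

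*Protocol article*

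**What the plan says.** Section 2.12 (Statistical methods) of the protocol article fixes the missing-data method. It states "For outcomes other than costs, multiple imputation assuming data Missing at Random will be performed", and adds that this is "performed using SAS PROC MI for variables with more than 10% missing data, incorporating covariates, intervention group, and cluster information". The same section fixes the analysis of continuous outcomes as "linear mixed-effects models with random intercepts for clusters to account for the hierarchical structure of the data".

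Section 2.8 (Sample size) gives the expected scale of missingness, planning 20% dropout on 25 recruited patients per cluster. The power statement rests on the patients who remain, on average 20 in each of the 20 circles, and reads "the study has 80.97% power to detect a between-group difference of 2.5 points on the RMDQ (SD = 6.0"). It takes an ICC of 0.05 and a two-sided 5% level.

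The article does not say in what form cluster enters the imputation model. Section 2.12 also lists Stata or R beside SAS as analysis software.

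**The concern.** An imputation model should reflect the structure that the analysis model estimates. Here the analysis separates between-circle from within-circle variation through a random intercept, and the comparison of arms is judged against the between-circle variation. PROC MI cannot fit a random intercept. Cluster can enter only as fixed indicators, through cluster-level covariates, or not at all. None of these reproduces the between-circle variance that the analysis then estimates from the completed data.

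The 6-month RMDQ is the primary patient-level outcome, and the planned 20% loss exceeds the 10% trigger, so the rule will apply to it if dropout is as planned. At stake is the width of its confidence interval, and with it the power of the superiority test and the exploratory non-inferiority analysis with its 2.5-point margin.

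**Working it through.** **Inputs (section 2.8).** 10 clusters per arm, 25 recruited and 20 observed per cluster, SD 6.0 (variance 36), ICC 0.05, difference 2.5, two-sided 5%. At ICC 0.05 the between-cluster variance is 0.05 × 36 = 1.8 and the within-cluster variance is 34.2.

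**The plan's own figure.** Design effect 1 + 19 × 0.05 = 1.95; effective size 200 / 1.95 = 102.6 per arm; SE = 6 × √(2/102.6) = 0.838. With a noncentral t on 18 df, power is 80.55%, close to the stated 80.97%. (The normal approximation gives 84.7%.) The total 400 / 0.8 = 500 also agrees.

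**Correct SE with 20 of 25 observed.** Variance of an observed cluster mean: 1.8 + 34.2/20 = 3.51. Variance of the arm difference: 2 × 3.51/10 = 0.702, SE 0.838.

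**Cluster as indicators, missing completely at random, no covariates.** Each missing value is drawn around its own cluster's observed mean. The 5 imputed values are one fifth of the cluster mean, so imputation adds 0.2² × (34.2/20 + 34.2/5) = 0.342 to the variance of each completed cluster mean.
- Within-imputation variance: 2 × (3.51 + 0.342)/10 = 0.770. The added noise appears here as extra between-cluster variance.
- Between-imputation variance: 2 × 0.342/10 = 0.068. The same noise appears again.
- Rubin's total with 15 imputations: 0.770 + (1 + 1/15) × 0.068 = 0.843, SE 0.918.
- Ratio 0.918 / 0.838 = 1.10. On 18 df this corresponds to a type I error of about 3.3% and power of about 75%.

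The noise is counted twice, which is why the error is conservative.

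**Group only, no cluster effect.** Imputed values are drawn around the arm mean with the full variance of 36.
- Within-imputation variance: 2 × (0.8² × 3.51 + 0.2² × 36/5)/10 = 0.507.
- Between-imputation variance: 2 × 0.2² × (36/50 + 36/200) = 0.072.
- Total: 0.507 + (1 + 1/15) × 0.072 = 0.584, SE 0.764.
- Ratio 0.764 / 0.838 = 0.91, type I error about 7.1%.

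**Simulation** (same inputs, random-intercept analysis, Rubin's rules, t with 18 df; 3,000 runs per scenario, and about 10,000 for comparing indicators with multilevel imputation):

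| RMDQ, ICC 0.05, 20% missing | Model SE / true SE | Type I error | Power |
|---|---|---|---|
| Mixed model, observed data | 1.00 | 5.1% | 80% |
| Cluster indicators | 1.10–1.11 | 2.9% | 73.5–75% |
| Group only | 0.91 | 6.6% | 85% |
| Multilevel, random intercept, group fixed | 1.00 | 4.8% | 81% |

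The higher power in the group-only row is bought with the inflated type I error. At 30% missing the ratios are 1.15 (indicators) and 0.88 (group only). The estimated difference is unbiased in every case.

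**With a covariate that predicts the outcome** (missingness depending on it, cluster-mean analysis), indicators give ratios of 1.05 and 1.07 in two runs at correlation 0.5 (type I error 3.1% and 3.5%), and 1.03 at correlation 0.75 (4.1%). These correlations are assumptions; the protocol gives none.

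**Imputing each arm separately** with the same single-level method does not cure it: 6% too large with indicators (3.5%), 10% too small without cluster (7.5%).

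**The case against.** The strongest reply is that the effect is modest, mostly on the safe side, and partly a matter for a statistical analysis plan that is not shown. Much of this stands. The protocol says cluster will be included, so the conservative direction is the main one; the too-narrow interval arises only if cluster enters weakly. The form of coding can properly be left to the analysis plan. Good auxiliary variables, such as earlier RMDQ scores, shrink the error even under single-level imputation. What does not fall away is that the article itself names a procedure that cannot fit the random intercept of its own analysis model, and no coding choice within that procedure supplies one.

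Four stronger readings are tempting and should not be drawn:
- **Aliasing.** Each circle lies in one arm, so 20 indicators plus group give 21 columns of rank 20. This does no harm in itself: imputation needs predictions, and the indicators already carry the group.
- **Twenty indicators as the only option.** Cluster-level covariates are another possible meaning of the planned cluster information.
- **Imaging.** A reader might infer that this primary outcome is equally affected. No binary outcome was simulated. Continuous-outcome runs at imaging's ICC of 0.01 and 20% missing gave standard errors 17–20% too large with indicators, but about right with group only (ratio 1.02). That indicates a direction at most, and whether imaging will exceed 10% missing is not known.
- **The 10% trigger.** It is a pre-stated rule, and no harm from it has been shown.

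**Conclusion.** The point holds for the 6-month RMDQ, at moderate size. With cluster indicators the standard error is roughly 5–10% too large at ICC 0.05, type I error is about 3–3.5%, and power without predictive covariates is about 73–75% against about 81%. With weak cluster information the standard error tends towards 10% too small and type I error towards 7%. The treatment estimate is not biased, and nothing here supports a claim that the plan as written inflates false positives.

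The figures assume equal clusters, 20% missing, the protocol's SD and ICC, and a continuous outcome. The larger indicator figures also assume values missing independently of covariates. The change should be made, but the trial does not fail without it.

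**What to change.** In section 2.12 and the analysis plan, replace PROC MI by multilevel multiple imputation with a random intercept for quality circle and group as a fixed effect. Use baseline and earlier RMDQ scores as auxiliary variables. R or Stata, both already allowed, can be used. The random-intercept, group-fixed form restored nominal behaviour in the simulation above; running multilevel imputation separately by arm, with only 10 circles each, was not tested and is not proposed.

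Alternatively, make the mixed model on observed data, with baseline covariates, the primary RMDQ analysis under missing at random, and keep imputation as a sensitivity analysis.

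Either change is one of wording, best made before unblinding. It costs a different package and a little more analysis work, with no effect on patients or data collection.
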